### Data collection

Baseline measurement (M0) is conducted before patients’ first contact in the outpatient clinic. Follow-up measurement (M1) is conducted 8 weeks after the intervention. The duration of a chemotherapy treatment varies from 3 to 6 months. The occurrence of chemotherapy side effects is individual and they are principally temporal being most severe in 3–7 days after each cycle. During the two-month follow-up period, patients have received four cycles of treatment, which is considered sufficient to assess the effects of the intervention. The researcher sends research information and baseline questionnaires (demographic data, PAM, knowledge test, FACT-C, NRS2002) to the patients with a return envelope enclosed. She contacts potential participants by phone before their first treatment to inform about the study and asks for their verbal consent. Patients return the questionnaires within a week before the first appointment in the outpatient clinic. In connection with this appointment, the researcher contacts the participants for verbal research info and written informed consent. Recruitment continues until the sample size is reached (40 + 40). The enrolment period will last 4–5 months based on calculated sample size and the assumption of 10 new CRC patients a week and that approximately 10% of the patients will refuse to participate. Outcome data is not collected on participants who suspend on their own initiative or deviate from intervention protocols. The researcher manages data confidentially by entering and storing data on a password-protected computer. Original study questionnaires are kept at the participating site. The researcher codes data for ease of data storage, review, tabulation, and analysis. Files in electronic and paper form will be discarded after the publication of the research results (2022). In the information letter, patients are instructed to report spontaneously any unintended effects to an outpatient clinic nurse. Nurses report these events to the physician and first author, who make the final decision to discontinue the study, if necessary. A formal data monitoring committee will not be set up due to the short duration of the study and the harms are known to be minimal.

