**Methods:**

An interdisciplinary expert group developed a face-to-face empowering educational intervention using teach-back method. A two-arm, single-centre, superiority trial with stratified randomisation (1:1) and pre-post measures will be used to assess the effect of the intervention compared to standard care. Patients (*N* = 40 + 40) will be recruited in one university hospital outpatient clinic in Finland. Eligibility criteria are adult patients diagnosed with colorectal cancer starting oral fluoropyrimidine or combination chemotherapy treatment. A registered nurse experienced in oncology will deliver the intervention 2 weeks after the first chemotherapy. Outcomes are measured before intervention (M0) and after a two-month follow-up period (M1).

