Due to the COVID-19 pandemic, the intervention was scheduled for the second chemotherapy course. The intervention will not entail any extra costs for patients. In case the intervention cannot be conducted face-to-face, it is possible to make it available online, e.g. as a video call.

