#### Side effects

Side effect self-monitoring is used to assess the intensity of the side effects as well as to reinforce the intervention effect by reflecting on the self-care activities. After the first chemotherapy treatment, nurses give the self-monitoring diary to patients in both IG and CG, to be returned to the researcher after the fourth (or the last) chemotherapy cycle. Patients in IG document the side effects and their intensity as they appear (NRS 0–10; 0 = not at all, 10 = the worst possible) before and after the performed self-care activities. In addition, patients document their individual expectations for additional knowledge, and this information is used during the educational intervention. Patients in CG only self-monitor and document the intensity of each side effect as it appears (NRS 0–10; 0 = not at all, 10 = the worst possible).

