#### Clinical data

Clinical data is gathered from electronic patients’ records. We are interested to find out whether the educational intervention is related to better adherence to treatment schedule. Therefore, data of patient-induced treatment changes, cancellations, transferring and interruptions are documented from baseline to 8 weeks. It has been indicated that worse nutritional status is related to greater morbidity [17]. Therefore, we collect data of patients’ emergency room visits and hospitalisation from baseline to 8 weeks.

The sample size was calculated to detect a 7-point mean difference in the PAM scale between groups assuming standard deviation of 11 points for both groups with 80% power and significance level of 0.05. This leads to required sample size of 40 participants per group. The meaningful difference between the average score of individuals who engage in healthy behaviours and those who do not is considered 4 points on the PAM scale [44]. To reach the target sample size (40 + 40), the researcher recruits participants by sending questionnaires with a research info and contacting them by phone the day before they visit the outpatient clinic. The researcher also meets the eligible participants to provide verbal information of the trial and answer questions. The strategies to improve patients’ adherence to the intervention protocol comprise the use of a self-monitoring diary and positive feedback from the research nurse. For individual participants, the intervention will be discontinued in the case of worsening condition, treatment change, or at their own request.

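### M1 is timed from the intervention session but clinical events are collected for 8 weeks from baseline, so event collection stops at least 2 weeks before M1 and the readable text gives controls no date from which to time M1

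*Protocol article*

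**What the plan says.** **Questionnaires.** Methods, Data collection: "Follow-up measurement (M1) is conducted 8 weeks after the intervention". The sentence does not separate the arms. The Abstract and the section on aim, design and setting speak only of two months of follow-up and do not say when it starts.

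**Clinical records.** Methods, Clinical data gives another origin, twice. Patient-induced treatment changes and "cancellations, transferring and interruptions are documented from baseline to 8 weeks"; the same section collects "emergency room visits and hospitalisation from baseline to 8 weeks".

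**Baseline.** Data collection places it before the patient's first contact with the clinic: "Patients return the questionnaires within a week before the first appointment in the outpatient clinic".

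**Session.** In the Abstract, the nurse "will deliver the intervention 2 weeks after the first chemotherapy". Under Intervention protocol: "Due to the COVID-19 pandemic, the intervention was scheduled for the second chemotherapy course".

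**Controls.** Under Standard care they receive standard education only, so they have no session and no session date.

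**The concern.** Two things follow from these statements.

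First, the M1 rule can be applied directly only to patients who had the session. Data analysis makes the between-arm comparison of M0-to-M1 change the main analysis, so the date of M1 bears on every primary and secondary outcome. By the article's own account, side effects are worst 3 to 7 days after each cycle, so the point in chemotherapy at which quality of life and nutritional risk are recorded is not neutral.

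Second, the clinical records are meant to show whether the education goes with better adherence to the treatment schedule and with fewer emergency visits and admissions. A window that opens before the session and closes before M1 includes time in which the session can have no effect, and omits the last weeks of the period over which the other outcomes are judged.

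**Working it through.** **Inputs.** M1 = session + 8 weeks (Data collection). Event window = baseline to baseline + 8 weeks (Clinical data). Session = first chemotherapy + 2 weeks (Abstract) or the second course (Intervention protocol). Baseline is before the first clinic contact (Data collection). Four cycles are given in the two-month follow-up (Data collection).

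**The article's own figures first.** Four cycles in 8 weeks is 8 / 4 = 2 weeks per cycle. On 2-week cycles, the two statements of the session date agree. They would part if cycles were longer, so a 3-week cycle is shown below as an assumption. The sample size is not touched by this point: a 7-point difference with SD 11, 80% power and two-sided 0.05 gives 39.75 per group by the t-test, hence the stated 40.

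**Calendar.** Let week 0 be first chemotherapy, c the cycle length and L the number of weeks by which baseline precedes first chemotherapy. L = 0 is the most favourable case; L = 1 is an assumption.

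- Session = c; M1 = c + 8
- Event window closes at 8 − L
- Gap to M1 = (c + 8) − (8 − L) = c + L
- Post-session weeks covered = (8 − L) − c

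| c | L | Session (week) | M1 (week) | M0 to M1 (weeks) | Window closes (week) | Gap (weeks) | Post-session weeks covered |
|---|---|---|---|---|---|---|---|
| 2 | 0 | 2 | 10 | 10 | 8 | 2 | 6 of 8 (75%) |
| 2 | 1 | 2 | 10 | 11 | 7 | 3 | 5 of 8 (62.5%) |
| 3 | 0 | 3 | 11 | 11 | 8 | 3 | 5 of 8 (62.5%) |
| 3 | 1 | 3 | 11 | 12 | 7 | 4 | 4 of 8 (50%) |

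The gap is 2 weeks at the least, and 2 to 4 weeks over the range shown.

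**What the dilution amounts to.** As an illustration only, suppose a true post-session rate ratio of 0.70, no effect before the session and a constant event rate; none of these is in the article. The apparent ratio is 1 − 0.30 × (share of the window after the session):

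- 75%: 1 − 0.30 × 0.75 = 0.78
- 62.5%: 1 − 0.30 × 0.625 = 0.81
- 50%: 1 − 0.30 × 0.50 = 0.85

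Treatment changes can hardly arise before treatment starts. If, with L = 1 and c = 2, only weeks 0 to 7 count, the share is 5 / 7 = 71% and the apparent ratio is 1 − 0.30 × 0.714 = 0.79.

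**Size of the M1 risk, if it occurred.** If controls were timed 8 weeks from first chemotherapy, they would answer at week 8 against week 10, with 4 cycles received against 5. If they were timed 8 weeks from a baseline one week before first chemotherapy, they would answer at week 7, which is 3 weeks or 3 / 2 = 1.5 cycles earlier. The article states neither rule.

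**The case against.** A reader might infer that the two arms are in fact measured at different points of chemotherapy, so that the quality-of-life and malnutrition comparisons are biased. The article does not support that. No section times control M1 from baseline; the baseline clock governs record extraction only. The Abstract and the aims describe one two-month follow-up for both arms, and giving controls the matching nominal date is a natural reading. The assessment schedule (Fig. 2) could not be seen, and it or the full protocol may fix the control date. This objection stands, and it reduces the arm-imbalance argument to a risk.

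The event window has the same origin and length in both arms, and that origin exists for controls, so it does not favour either arm. The records it governs are supporting data and are not among the named primary or secondary outcomes. Both points stand and limit the weight of the finding. The rate-ratio figures rest on assumed inputs and only illustrate scale.

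It may also be said that the baseline-to-8-weeks wording is shorthand for M0 to M1. That does not remove the mismatch: on the stated times M0 to M1 is at least 10 weeks, so under that reading Clinical data and Data collection contradict each other.

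Finally, the diary is "to be returned to the researcher after the fourth (or the last) chemotherapy cycle". One could ask for it to run to M1, but its stated purpose is to record side-effect intensity and reinforce self-care, and nothing ties it to M1. It is not a defect.

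**Conclusion.** The two 8-week clocks are both in the text and do not fit together. With the session 2 weeks after first chemotherapy, event collection ends at least 2 weeks before M1 and covers at most 6 of the 8 post-session weeks. Coverage is 5 of 8 if baseline is assumed to be one week before first chemotherapy, and 4 of 8 if a 3-week cycle is assumed as well. The effect is to weaken the adherence and morbidity comparison, not to tilt it towards one arm.

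Separately, the rule for M1 rests on a date that controls and intervention patients without a session lack, and the readable text offers no substitute. That is a gap in the rule as written. It is not evidence that M1 differed between arms.

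**What to change.** Reconcile Clinical data and Data collection to one time origin:

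1. Time M1 in both arms from one date that exists for every randomised patient, with the same permitted window. First chemotherapy plus 10 weeks would match the nominal session date plus 8 weeks (2 + 8 = 10). For anyone randomised who does not start chemotherapy, the randomisation date can serve as the origin.
2. Extract treatment changes, emergency visits and hospitalisations for all randomised patients from randomisation or first chemotherapy through M1. Some pre-session time stays in the count, as it should when patients are analysed as randomised: on the nominal dates, 8 of the 10 weeks from first chemotherapy (80%) follow the session, and all 8 post-session weeks are covered.
3. Report the actual number of days from M0 to M1 by arm. This shows whether the timing risk arose.

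Events should not be counted from the second chemotherapy visit. Patients who stop before it would have no reference date, and events after randomisation would be set aside, although early stopping is part of what these data are meant to capture.

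The cost is a change of wording and 2 to 4 more weeks of record extraction per patient, with no extra visit and no change to the 40 per group.

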### Assignment of interventions

The researcher (LT) enrols the participants, and those willing to participate are randomly assigned to CG and IG using stratified randomisation according to stage of disease and existence of stoma. An allocation sequence using blockrand package [54] in R version 3.6.1 [55] was used. For each block, the block size was randomly chosen from a set of 2, 4 and 6. Allocation ratio of 1:1 was used. The statistician generated an unpredictable allocation sequence using sequentially numbered, opaque, sealed envelopes. The envelopes, numbered in advance, are opened sequentially after the participant’s name is written on the appropriate envelope [56]. The researcher (LT) allocates participants to the intervention with equal probability as a simple random sample is drawn from each group. Thus, the person enrolling participants does not know in advance which treatment the next person will get [39]. Patients' blinding is not possible as the RN informs the patients in IG of the one-hour educational session. The research nurse cannot be blinded because she provides the intervention. The data analyst is blinded as data are anonymised by using codes (001, 002 etc.).

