### Data analysis

Statistical methods are used for analysing primary and secondary outcomes between the two groups and related factors. The main analysis is to compare the change from M0 to M1 in primary outcomes (patient activation and knowledge level) and secondary outcomes (QoL and risk of malnutrition) between IG and CG. Categorical variables will be described using frequencies and percentages. Continuous variables will be expressed as means with standard deviations for normally distributed variables and medians with interquartile ranges for non-normally distributed variables. The differences in changes between groups in continuous outcomes will be compared with two-sample t-test or Mann-Whitney U-test and the changes within groups with paired t-test or Wilcoxon signed rank test, as suitable. Logistic regression using generalised estimating equation (GEE) will be used to test the differences between and within groups at risk of malnutrition (classified as 0–2 and 3–7). Results will be presented using estimates of group differences with 95% confidence intervals. The effect of missing data on the results will be examined using sensitivity analysis. An intent-to-treat analysis will be applied and two-sided statistical tests with significance level of 0.05 will be used in the statistical analyses. Methods for any additional analyses are determined by the data.

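### The 40 per group needed in the analysis is also the recruitment stop, so the stated 80% power holds only if no patient is lost

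*Protocol article*

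**What the plan says.** The calculation stands in the Clinical data section of the protocol article: "The sample size was calculated to detect a 7-point mean difference in the PAM scale between groups". Its other inputs are an SD of 11 in each arm, 80% power and alpha 0.05. Its result: "This leads to required sample size of 40 participants per group". The Data analysis section makes the tests two-sided ("two-sided statistical tests with significance level of 0.05 will be used in the statistical analyses"), and Assignment of interventions gives the ratio: "Allocation ratio of 1:1 was used".

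The same number is then used for enrolment. The Methods part of the abstract describes 40 + 40 as patients to be recruited, the Clinical data section calls it the target for recruitment, and Data collection sets the stop: "Recruitment continues until the sample size is reached (40 + 40".

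Three further statements bear on how many patients reach the analysis:
- For individual participants, "the intervention will be discontinued in the case of worsening condition, treatment change, or at their own request" (Clinical data).
- Outcome data are not gathered on participants who suspend on their own initiative or deviate from the protocol (Data collection).
- The main analysis compares the M0-to-M1 change between groups, under intent-to-treat, with an unspecified sensitivity analysis for missing data (Data analysis).

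**The concern.** A sample size formula returns the number of patients with an analysable outcome. When recruitment stops at that number, every missing outcome comes out of the power. Here the protocol itself foresees missing outcomes, because it declines to collect them from some participants, and its change-score analysis needs both measurements.

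What is at stake is how the result will be read. A reader who takes 80% at face value will give a non-significant primary result slightly more weight as evidence against a 7-point effect than the design supports. The rule on outcome collection also sits badly with the intent-to-treat commitment, since intent-to-treat cannot supply outcomes that nobody sought.

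**Working it through.** **Inputs.** Difference 7, SD 11, power 80% and alpha 0.05 (Clinical data); two-sided (Data analysis); 1:1 (Assignment of interventions). The loss rate is not given, so 5% to 20% is assumed.

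**Step 1: reproduce the 40.** Normal approximation: n = 2 × [11 × (1.960 + 0.842) / 7]² = 38.76, so 39 per arm. Two-sample t-test (noncentral t, d = 7/11 = 0.636): n = 39.75, so 40 per arm. A one-sided test would give 31. The protocol's figure is therefore the two-sided t-test result with nothing added for loss.

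**Step 2: power when fewer than 40 are analysed.** The noncentrality is 0.636 × √(n/2), with 2n − 2 degrees of freedom.

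| Assumed loss | Analysed per arm | Power for 7 points |
|---|---|---|
| 0% | 40 | 80.3% |
| 5% | 38 | 78.2% |
| 10% | 36 | 75.9% |
| 15% | 34 | 73.4% |
| 20% | 32 | 70.7% |

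One patient lost in the whole trial (40 against 39) gives 79.7%.

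**Step 3: what SD 11 refers to.** The calculation speaks of the PAM scale; the analysis is of change. If 11 is the SD of the score, with the same SD at both times and baseline-to-follow-up correlation r, the SD of the change is 11 × √(2(1 − r)). This equals 11 only at r = 0.5.
- r = 0.4: SD of change 12.05, power 73% at 40 per arm with no loss at all.
- r = 0.6: SD of change 9.84, power 88% at 40 per arm and 80% at 32 per arm.

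The table in step 2 therefore holds if 11 is the SD of the change, or if it is the score SD and r = 0.5.

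**Step 4: adjusting for baseline.** With 11 as the score SD, analysis of covariance has residual SD 11 × √(1 − r²). With 32 analysed per arm:

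| r (assumed) | Residual SD | Power |
|---|---|---|
| 0.3 | 10.49 | 75% |
| 0.5 | 9.53 | 82% |
| 0.7 | 7.86 | 94% |

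If 11 is instead the SD of the change, the residual SD becomes 11 × √((1 + r)/2), which is still below 11 for any r under 1.

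**The case against.** The strongest reply is that nothing has been miscalculated. Forty is the right answer to the question asked, and the article condenses a fuller protocol that may discuss attrition. The first half stands: the arithmetic is correct. The second half does not remove the point, because the article does more than leave out a rate. It states the calculation and the recruitment stop, and the two coincide exactly at zero loss. The recruitment sentence in Data collection, read alone, could mean completers, but the abstract and the Clinical data section speak of recruiting 40 + 40. The 10% in Data collection is refusal before enrolment and is used for the length of the enrolment period, so it is no allowance for loss.

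A second objection is that the shortfall is small and assumed. This largely stands. Follow-up is 8 weeks after a single session, 5% loss costs about 2 points of power, and the drop becomes clear only from about 10%. Stopping the intervention is also not the same as losing M1: a worsening condition or treatment change need not remove the outcome. The direct source of loss is the rule on not collecting outcomes.

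Third, the planned confidence intervals will show whatever imprecision results. That is true and limits the harm, but it does not make the stated power correct.

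A reader might also infer that the trial is badly underpowered for the 4 points mentioned beside the calculation. The document does not support this. There, 4 points separates the average scores of people who do and do not engage in healthy behaviours. It is not given as the between-arm effect this trial aims to detect. Powering for 7 is a design choice, and no rule about confidence intervals that include 4 follows from the text.

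**Conclusion.** The point holds in a limited form. The calculation is right, but it gives the number to be analysed, and the protocol recruits exactly that number while providing for missing outcomes. The stated 80% is the zero-loss value. With assumed losses of 5%, 10% and 20%, power for 7 points is about 78%, 76% and 71%.

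These figures rest on two things the protocol does not settle: the loss rate, and SD 11 being the SD of the analysed quantity (or r = 0.5). One might be tempted to conclude that the trial certainly lacks its stated power. The documents do not support that, since with 11 as the score SD and r = 0.6 even 20% loss leaves about 80%. What they do show is that the figure has no reserve and that its basis is unclear.

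**What to change.** 1. Restate the sample size sentence along these lines: 40 analysed per group give 80% power for a 7-point difference; with 80 randomised and an assumed 10–20% without M1, power is about 76–71%. This is wording only.
2. Say whether SD 11 is the SD of the PAM score or of its change. Also wording only.
3. Seek M1 from all randomised patients, including those who suspend or deviate, unless they decline follow-up. The intent-to-treat analysis requires this. The cost is some follow-up effort.
4. Analyse M1 PAM adjusted for baseline PAM in place of the unadjusted change-score test. Baseline PAM is already collected, so no new data are needed, but this changes the primary analysis and should be recorded as an amendment before the data are analysed. Quote the gain as conditional: with 32 analysed per arm and 11 as the score SD, about 75%, 82% or 94% power at r = 0.3, 0.5 or 0.7.

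If the sponsor would rather keep 80% without relying on r, the alternative is to randomise 40/(1 − loss) per arm: 40/0.9 = 44.4, so 45 at 10% loss, or 40/0.8 = 50 at 20%. The article describes recruitment as still under way. This costs 10 to 20 more patients in total.

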#### Intervention protocol

The intervention was developed during autumn 2018 and spring 2019 by an interdisciplinary expert group consisting of two RN experienced in oncology, a clinical nutritionist, an oncologist, and the researcher (LT). We held four shared meetings and additional discussions between each member and the researcher. According to the protocol, patients in IG will receive knowledge of healthy diet and malnutrition. In addition, they will receive tailored knowledge of NIS. The tailoring is based on the side effect self-monitoring diary and patient activation level assessment according to the Patient Activation Measure (PAM) [35]. In addition, patients receive knowledge of the prevention of NIS and self-care strategies based on organisation guidelines. The teach-back method is used to verify participants’ understanding of the received knowledge, to tailor education, to uncover health beliefs, and to activate patients in dialogue [36]. Participants have to be able to teach back the main parts of the knowledge related to malnutrition as well as the reasons, prevalence, and self-care of the NIS they are suffering from. The teach-back method has shown a positive effect in self-care by improving outcomes in disease-specific knowledge, adherence and self-efficacy among people with chronic disease. It has also reduced hospital readmission rates [37].

Empowerment is supported by offering additional knowledge according to patients’ expectations. In addition, the research nurse uses active listening and strengthening self-care strategies that have been successful. The progression of the discourse is based on patients’ expectations and active involvement: the nurse provides the patient with expert knowledge and maintains an empathic connection to the patient throughout the session [38].

The content of the educational intervention is as follows:
Illustrating the purpose of the session.Exploring patients’ current knowledge of healthy diet and malnutrition, offering additional knowledge using teach-back.Bringing forward individual NIS and their intensity on a numerical rating scale (NRS) ≥3, and patients’ knowledge expectations, offering additional knowledge using teach-back.Bringing forward performed self-care strategies and offering additional knowledge using teach-back.Bringing forward individual NIS and their intensity (NRS < 3), offering additional knowledge.Making a brief summary.

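### Not collecting outcomes after self-suspension or deviation contradicts the intent-to-treat statement and leaves a main analysis of adherent completers

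*Protocol article*

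**What the plan says.** The Data collection section of the protocol article states: "Outcome data is not collected on participants who suspend on their own initiative or deviate from intervention protocols". It times M1 at 8 weeks after the intervention and ends recruitment once 40 + 40 participants are reached.

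The Data analysis section states: "An intent-to-treat analysis will be applied and two-sided statistical tests with significance level of 0.05 will be used". The main comparison is of the M0-to-M1 change between groups, by two-sample t-test or Mann-Whitney test for continuous outcomes. On incomplete data it says only: "The effect of missing data on the results will be examined using sensitivity analysis".

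Two other places bear on who might be affected. The sample-size paragraph, under Clinical data, says that for individual participants "the intervention will be discontinued in the case of worsening condition, treatment change, or at their own request". The Intervention protocol section describes the education for the intervention group: "According to the protocol, patients in IG will receive knowledge of healthy diet and malnutrition". Under Standard care, both groups receive standard education.

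**The concern.** Intent-to-treat means that everyone randomised is analysed in the arm assigned, whatever happened afterwards. The collection rule makes measurement of the outcome depend on behaviour after randomisation. Those who stop or deviate then differ from those who remain in ways that may relate to activation, knowledge, quality of life or malnutrition risk, and the balance that randomisation gave is no longer assured.

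Both primary outcomes depend on this rule. The Discussion section says that recruitment is under way, and an 8-week outcome that was not measured at the time cannot be measured later. The sample-size statement shows no allowance for lost outcomes, so any loss also lowers power.

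**Working it through.** **1. The two statements side by side.** The planned test needs a change score, M1 minus M0. Under the collection rule, a participant who suspends or deviates has no M1 and so no change score. That person drops out of the t-test or Mann-Whitney comparison although randomised. The participants left are those who stayed and adhered. The two statements cannot both be followed on observed data.

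**2. Which arm the rule reaches.** The rule has two parts. Suspending on one's own initiative is possible in either arm. Deviating from intervention protocols falls mainly on the intervention group, because its education protocol is the one described.

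**3. The plan's own figure.** Inputs from the sample-size paragraph: difference 7 PAM points, SD 11, 80% power, significance level 0.05 (two-sided, from Data analysis).
- Normal approximation: n = 2 × [11 × (1.960 + 0.842) / 7]² = 38.8, so 39 per group.
- Exact t-test: 39.75, so 40 per group, with 80.3% power at 40.

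The stated 40 per group is reproduced and is not in dispute. It holds only with M1 on all 80.

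**4. Bias formula.** Let f be the share of an arm left unmeasured and g the shortfall in mean PAM change of those people against the rest of their arm. If the measured mean is m, the full-arm mean is (1 − f) × m + f × (m − g) = m − f × g. The measured mean is therefore too high by f × g. With the same g in both arms, the bias in the group difference is (f in intervention − f in control) × g.

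The document gives neither f nor g. **Assumed here:** f = 10-20% and g = 4-11 points. The 4 is the difference that the protocol calls meaningful, and the 11 is its assumed SD.

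**5. Three scenarios.** Power is for a true 7-point difference, by t-test, with the bias itself left out.

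| Scenario | Analysed (intervention / control) | Bias, PAM points | Power |
|---|---|---|---|
| Loss in intervention only, 10% | 36 / 40 | 0.10 × 4 = +0.4 to 0.10 × 11 = +1.1 | 78.1% |
| Loss in intervention only, 20% | 32 / 40 | 0.20 × 4 = +0.8 to 0.20 × 11 = +2.2 | 75.4% |
| Equal loss and prognosis, 10% | 36 / 36 | 0 | 75.9% |
| Equal loss and prognosis, 20% | 32 / 32 | 0 | 70.7% |
| Intervention 10%, control 20% | 36 / 32 | (0.10 − 0.20) × 4 = −0.4 to (0.10 − 0.20) × 11 = −1.1 | not calculated |

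**6. False-positive rate, intervention-only loss, no true effect.** The standard error is 11 × √(1/36 + 1/40) = 2.53 at 10% loss and 11 × √(1/32 + 1/40) = 2.61 at 20%. A bias of 0.4 to 1.1 points at 10% loss gives rejection in 5.3% to 7.1% of trials. A bias of 0.8 to 2.2 points at 20% loss gives 6.1% to 13.2%. The nominal rate is 5%.

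**The case against.** A reader might infer more: that the rule turns the trial into a one-sided per-protocol comparison biased towards the intervention. The document does not support that.

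- **One-sided.** Self-suspension applies to both arms. Even the deviation part is not defined. The text speaks of intervention protocols in the plural, standard care for both groups sits under the Intervention heading, and the control group has its own diary procedure under Side effects.
- **Direction.** No withdrawal rate, deviation rate or prognosis is given. Control patients, who get no extra session, could withdraw more often, and the sign would then reverse.
- **Failed teach-back.** The Intervention protocol section says: "Participants have to be able to teach back the main parts of the knowledge related to malnutrition". It presents teach-back as a way to verify understanding and tailor the education. It does not make failure a deviation.
- **Worsening condition.** The reasons for stopping the intervention include worsening condition and treatment change. Only own request clearly matches the collection rule. Nothing says that the other two end data collection.
- **Size.** The intervention is a single session of about an hour, so deviation may be uncommon. Power falls with any attrition, not only with this rule.

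All of these points stand. It is also fair to say that an analysis by assigned arm remains possible with imputation, that M0 is available for it, and that such detail commonly sits in an analysis plan that is not shown here. But imputation would rest on untestable assumptions about people whom the trial chose not to measure. The planned sensitivity analysis cannot supply their outcomes. The contradiction lies in data collection, and an analysis plan cannot repair it.

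**Conclusion.** The contradiction is real and should be fixed. Followed as written, the collection rule removes randomised participants from the main analysis because of what they did after randomisation, and the result would carry an intent-to-treat label that it had not earned.

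The consequence is a risk of bias, plausibly in favour of the intervention because the deviation part falls mainly on that arm, but with size and direction unknown. Under the assumptions shown, the bias could be trivial, or it could reach 2.2 points, a little over half of the 4-point difference that the protocol calls meaningful. It could also be zero or negative. The bias figures for intervention-only loss belong with the power figures of 78.1% to 75.4%. The power figures of 75.9% to 70.7% belong to equal loss, where there is no bias. The two harms should not be added together. No estimate is offered for knowledge, quality of life or malnutrition risk.

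**What to change.** Replace the sentence in Data collection with a rule such as: *M1 outcomes and records data are sought for every randomised participant, whether or not the session was received or completed, unless consent to data collection is withdrawn. All participants are analysed in the arm assigned.*

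Two additions are needed:
- Set an M1 date for participants without a session, because M1 is timed from the intervention.
- Record deviation as a variable, and use it only for a supportive per-protocol analysis.

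The cost is one amended sentence and a small number of extra M1 questionnaires. At the assumed 10-20% loss this is 4 to 8 if only the intervention group is affected (0.10 × 40 to 0.20 × 40), or 8 to 16 if both are. Baseline questionnaires already come with a return envelope, and clinical data come from electronic records. How M1 is delivered is not stated, so the use of post for it is an assumption. Some who suspend may also withdraw consent to data collection. Their outcomes will stay missing and should be reported as such.
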